## Abstract

**Background:**

Graft survival after kidney transplantation has significantly improved within the last decades but there is a substantial number of patients with declining transplant function and graft loss. Over the past years several studies have shown that metabolic acidosis plays an important role in the progression of Chronic Kidney Disease (CKD) and that alkalinizing therapies significantly delayed progression of CKD. Importantly, metabolic acidosis is highly prevalent in renal transplant patients and a recent retrospective study has shown that metabolic acidosis is associated with increased risk of graft loss and patient death in kidney transplant recipients. However, no prospective trial has been initiated yet to test the role of alkali treatment on renal allograft function.

**Methods:**

The Preserve-Transplant Study is an investigator-initiated, prospective, patient-blinded, multi-center, randomized, controlled phase-IV trial with two parallel-groups comparing sodium bicarbonate to placebo. The primary objective is to test if alkali treatment will preserve kidney graft function and diminish the progression of CKD in renal transplant patients by assesing the change in eGFR over 2 years from baseline. Additionally we want to investigate the underlying pathomechanisms of nephrotoxicity of metabolic acidosis.

**Discussion:**

This study has the potential to provide evidence that alkali treatment may slow or reduce the progression towards graft failure and significantly decrease the rate of end stage renal disease (ESRD), thus prolonging long-term graft survival. The implementation of alkali therapy into the drug regimen of kidney transplant recipients would have a favorable risk-benefit ratio since alkali supplements are routinely used in CKD patients and represent a well-tolerated, safe and cost-effective treatment.

**Trial registration:**

ClinicalTrials.gov NCT03102996. Trial registration was completed on April 6, 2017.

## Background

The treatment of end-stage chronic kidney disease includes hemodialysis, peritoneal dialysis and kidney transplantation (KTx), while today KTx is the treatment of choice due to better survival, quality of life and cost effectiveness in comparison to maintenance dialysis [1, 2]. Short- and long-term graft survival after KTx have significantly improved within the last decades but there is still a substantial number of patients with declining transplant function and graft loss in the long term. Currently, the mean 20-year graft survival is only 30–40% [3]. Consequently, there is a clear need to develop and test for new therapies that may help to preserve long-term graft function. In addition, identification of reliable candidate biomarkers would allow predicting long-term allograft function or select specific transplant patients that may benefit from new strategies.

Metabolic acidosis (MA) is a well-known complication of CKD and associated with a variety of complications such as uremic bone disease, protein-energy wasting, chronic inflammation, insulin resistance, impairment of myocardial function and disturbances in mineral metabolism, growth hormone and thyroid gland function [4–6]. In addition, observational studies have shown that MA is associated with increased mortality in both, dialysis patients and patients with non-dialysis dependent CKD [7]. Importantly, MA is highly prevalent in renal transplant patients with prevalences reported ranging from 12 to 58% and seems to be consistently more frequent and more severe when compared to non-transplant CKD cohorts with similar degrees of renal function [8–10]. In our clinic, a cross-sectional analysis among 823 unselected kidney transplant patients revealed metabolic acidosis in 58.1% of the patients defined by a serum bicarbonate of < 24 mmol/l indicating a high prevalence of MA in this patient cohort [8]. Notably, eGFR correlated best with serum bicarbonate levels at time of examination. These data could be confirmed by other authors [9] and similar to CKD patients creatinine clearance was markedly lower in the group of transplant patients with MA compared to the non-acidotic patients. Over the past few years several studies have shown that MA plays an important role in the progression of CKD and that low serum bicarbonate levels are associated with a higher risk of progressing to end-stage renal disease [5, 7, 11–15]. Amelioration of MA in CKD patients with alkalinizing therapies delayed progression of GFR loss [16–18]. Furthermore, a recent study has shown for the first time that MA after KTx is associated with increased risk of graft loss and patient death as mentioned before for CKD patients. In this multicenter retrospective cohort study of 2318 patients, a low TCO_2_ level (< 22 mmol/L) 3 months after transplantation was associated with increased risk of graft loss and death-censored graft failure even after adjusting for eGFR [19]. However, to the best of our knowledge, no prospective trial has been initiated yet to test the role of alkali treatment in the prevention of progressive loss of renal allograft function.

Apart from the crucial question if alkali treatment may have a beneficial effect on graft function there are at least two other important aspects of metabolic acidosis after kidney transplantation that are not fully understood yet, namely first the underlying pathomechanisms why MA occurs in KTx patients and second how metabolic acidosis may promote disease progression. It has been reported that MA is more common in patients who received a cadaveric organ compared to a transplant from a living donor [20] but as of today, the influence of donor age, donor renal function and further pre-transplant factors on the occurrence of MA after KTx is still unclear [10]. Other factors such as the intake of calcineurin inhibitors have been shown to be associated with the development of MA by specific changes in tubular epithelial cells which play a role in acid-base regulation [8, 20–24]. In CKD, Wesson et al. investigated intensively the pathogenic effects of endothelin, aldosterone and angiotensin-II on the kidney and its impact on GFR [13, 14, 17, 25–28]. Likewise, a role of the complement system and accumulation of interstitial ammonium had been early proposed to contribute to progression of CKD [29]. Thus, it is essential to investigate the role and in particular the pathomechanisms of MA on graft function and outcome. These findings may help to develop new potential therapeutic targets, such as alkali therapy, that may help to preserve long-term graft survival in this population.

To date, more than 3000 patients with a functioning kidney transplant are living in Switzerland and over 200,000 in the United States [30]. Many of these patients already suffer from decreased graft function which favours the development of MA. Given the expanding pool of CKD patients - including former kidney transplant recipients - an alkali treatment study in kidney transplant patients is of prime importance and has the potential to show that such a treatment may slow or reduce the progression towards graft failure and significantly decrease the rate of end stage renal disease, and therefore prolonging long-term graft survival in KTRs.

## Methods

### Trial design

The Preserve-Transplant Study (PTS) is an investigator-initiated, prospective, patient-blinded, multi-center, randomized, controlled phase-IV trial with two parallel-groups comparing sodium bicarbonate to placebo. The study encompasses 300 patients, ≥ 18 years of age, at least 12 months after renal transplantation and with a serum bicarbonate level ≤ 22 mmol/l. A placebo was chosen as a comparator to the intervention because no equivalent active comparator is existing to date that would qualify as an appropriate comparator. Participants will be randomly allocated to receive sodium bicarbonate or placebo in a 1:1 distribution and will be followed up for 2 years (see Fig. 1). The trial is performed at three transplant centers in Switzerland, in Zurich, Berne and Geneva.

**Fig. 1 Fig1:**
[figure not shown]
Study Flowchart of the Preserve-Transplant Study. Numbers in circles define each study visit. Study visits 2, 7, and 11 include in addition to blood and spot urine tests 24 h-ambulatory blood pressure monitoring and 24 h urine collection

### Objectives and hypothesis

The primary objective of PTS is to test if alkali treatment will preserve kidney graft function and diminish the progression of chronic kidney disease in renal transplant patients by assesing the change in eGFR over 2 years from baseline compared to placebo.

Additionally we want to investigate underlying pathomechanisms of metabolic acidosis and how metabolic acidosis may promote disease progression. A further objective is to identify reliable candidate biomarkers that would allow selecting specific transplant patients that may benefit from alkali therapy.

This study assesses long-term safety of the study drug with a particular focus on new onset and worsening of hypertension, volume overload, and gastrointestinal side effects. Selected adverse events (AEs) and all serious adverse events (SAEs) will be documented regularly and compared between the treatment and placebo group.

### Trial outcomes

The primary outcome of this study is the change in renal function by assessing eGFR within 2 years. eGFR will be determined based on the CKD-EPI creatinine equation. By now, eGFR is the best parameter to assess kidney function and to predict graft and patient survival in kidney transplant recipients [1]. Recent recommendations from the NKF-FDA Scientific Workshop and other publications show that eGFR decline over 2–3 years is an acceptable endpoint for CKD progression trials and clinical transplant research [1, 31–33]. Additionally, several recent studies have used eGFR successfully to investigate the effect of alkali treatment on progression of chronic kidney disease [13, 14, 28]. Moreover, creatinine is a well-established, standardized, and reliable parameter ubiquitously measured in routine clinical practice and compared to inulin or radiolabeled isotopes such as ^125^I Iothalamate or ^51^Cr EDTA very cost-effective and easy available.

Important secondary outcomes include changes in serum bicarbonate levels, pH, sodium, potassium, and proteinuria measured as protein/creatinine or albumin/creatinine ratio in spot urine. As a safety outcome, 24-h ambulatory blood pressure monitoring will be performed at the beginning of the study and after 1 and 2 years to evaluate the effect of sodium bicarbonate on blood pressure. All outcomes of interest are shown in Table 1**.**

**Table 1 Tab1:** Study Outcomes

Primary Outcome	Change in renal function by assessing eGFR (CKD-EPI) within 2 years
Important Secondary Outcomes	Changes in serum bicarbonate levels, pH, sodium, potassium, and proteinuria measured as protein/creatinine or albumin/creatinine ratio in spot urine
Safety Outcome	Twenty-four-hour ambulatory blood pressure monitoring will be performed at the beginning of the study and after 1 and 2 years
Other Outcomes of Interest	• Changes in measurement of specific acid base transport proteins by urinary exosome collection • Changes in urinary ammonium excretion, inflammatory markers such as complement factors, and hormones involved in tubulo-interstitial nephritis/fibrosis such as endothelin and aldosterone • Histopathological grade of tubulo-interstitial fibrosis according to BANFF classification in kidney biopsies (where available) will be analyzed in both arms • Systemic calcification propensity in blood will be determined by the *T*_*50*_-Test (A test measuring the transformation time (*T*_*50*_) of primary to secondary calciprotein particles, where a long delay of *T*_*50*_ indicates a high residual capacity of the patients’ serum to prevent the formation of secondary calciprotein particles and is therefore a sign of an intact endogenous defense against calcification) [34] • Change of bone density and rejection rate

### Study population

Kidney transplant patients will be recruited from all study centers according to the inclusion and exclusion criteria (Table 2).

**Table 2 Tab2:** Inclusion and Exclusion Criteria of the Preserve-Transplant Study

Inclusion Criteria	
• Informed consent as documented by signature	
• Age ≥ 18 years and able to give informed consent	
• ≥ 12 months after renal transplantation	
• Stable clinical condition	
• Stable graft function over the last 6 months (creatinine changes ±15%)	
• eGFR between 15 and 89 ml/min/1.73 m^2^	
• At least one serum bicarbonate measured ≤22 mmol/l within the last 6 months	
Exclusion Criteria	
• Uncontrolled hypertension or use of > 4 antihypertensive agents	
• Uncontrolled heart failure	
• Serum potassium < 3.0 mmol/l	
• Serum sodium > 150 mmol/l	
• Use of alkali in the preceding 4 weeks	
• Use of mineralocorticoid antagonists, topiramate, carbo anhydrase inhibitors or any drugs with similar effects	
• History of noncompliance with clinic visits	
• Hereditary fructose intolerance	
• Known hypersensitivity or allergy to the drug used in this study or to peanut, sorbitol, and soy	
• Pregnancy or breastfeeding	
• Intention to become pregnant during the course of the study	
• Lack of safe contraception, defined as: Female participants of childbearing potential, not using and not willing to continue using a medically reliable method of contraception for the entire study duration, such as oral, injectable, or implantable contraceptives, or intrauterine contraceptive devices, or who are not using any other method considered sufficiently reliable by the investigator in individual cases. Please note that female participants who are surgically sterilised / hysterectomised or post-menopausal for longer than 2 years are not considered as being of child bearing potential.	
• Suspected drug or alcohol abuse	
• Inability to follow the procedures of the study, e.g. due to language problems, psychological disorders, dementia, etc. of the participant	
• Enrolment of the investigator, his/her family members, employees and other dependent persons	

### Study enrolment, randomization and blinding

Potential candidates will be identified from the electronic hospital databases. After signature of the informed consent and successful screening patients will be randomized in a 1:1 ratio stratified by each study center and gender using a permuted block design. The block size will be concealed until the primary endpoint will be analyzed. The randomization lists remain within the electronic data management tool for the whole duration of the study. Thus, randomization will be conducted without any influence of the principal investigators or other study personnel. The study is single-blind on the patient side.

### Biobank

Biobank samples are obtained at every study visit in all study centers and stored at − 80 °C for 5 years after termination of the study according to Swiss legal requirements. All samples or genetic data will be stored and used for future research purposes with the participant’s consent.

### Investigational medicinal product

Nephrotrans® (sodium hydrogen carbonate, ATC-Code: A02AH) has been approved and used since 1986 for the treatment of metabolic acidosis. Nephrotrans® is a safe, well-tolerated drug with very few and well-studied side effects. The study drug will be provided by SALMON Pharma GmbH in its commercially available formulation, used orally in this study and will be given at an initial dose of 500–1000 mg sodium hydrogen carbonate thrice daily. The dosage is chosen according to the body weight of the patient at baseline visit (< 70 kg or ≥ 70 kg). If serum bicarbonate remains ≤22 mmol/l the dosage of sodium hydrogen bicarbonate will be titrated once to 1000–1500 mg thrice daily as for placebo too at visit 3 after 2 weeks. All patients will be blinded to the identity of the study drug. The study product will be administered for a total of 2 years. The placebo is also provided by SALMON Pharma GmbH and used as a comparator to the intervention in this study. All patients will have the best standard care for kidney transplant patients.

### Informed consent

Written informed consent for participation will be obtained from all participants before any study related actions are taken. Patients will be informed that withdrawal from the study is possible at any time without giving reasons.

### Approvals

The study has been approved by the Cantonal Ethics Committee of Zürich, Berne and Geneva and Swissmedic as the competent authority. The study has been registered on ClinicalTrials.gov (NCT03102996). The project will be conducted in line with the Declaration of Helsinki as well as all national legal and regulatory requirements. In addition all researchers will follow the GCP guidelines. All non-substantial and substantial amendments of the protocol will be reported to the ethics committees and the competent authorities in Switzerland.

### Criteria for discontinuation

Patients will be withdrawn from participation in the trial if they withdraw their consent or the investigator or sponsor withdraws the patient because of malcompliance with the study intervention. Additionally, if serum bicarbonate exceeds 35 mmol/l or falls below 16 mmol/l the patient will have to be excluded from the study for safety reasons. Pregnancy in women or a significant violation of the protocol as judged by the coordinating investigator also will lead to withdrawal of the participant. Patients will be withdrawn from study treatment permanently if a severe allergic or hypersensitivity reaction to the drug occurs or if the investigator feels that the treatment is harmful to the subject. In case of a treatment-related SAE the study drug will also be withdrawn from the patient. A study patient who discontinues study participation prematurely for any reason is defined as dropout if the subject has already been randomized. A study patient who terminates the study before randomization is regarded as a screening failure.

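### Entry has no lower serum bicarbonate limit, yet the discontinuation rule requires exclusion below 16 mmol/l, so a patient can be randomised while already in the range the plan treats as unsafe

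*Protocol article*

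**What the plan says.** All references are to the protocol article.

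- **Entry, Table 2 (Study population).** The bicarbonate criterion is "At least one serum bicarbonate measured ≤22 mmol/l within the last 6 months". It is an upper limit on a value that may be months old.
- **Entry, Trial design.** The population is described as "at least 12 months after renal transplantation and with a serum bicarbonate level ≤ 22 mmol/l". Again there is only an upper limit.
- **Exclusions, Table 2.** Two laboratory values are bounded: "Serum potassium < 3.0 mmol/l" and "Serum sodium > 150 mmol/l". Bicarbonate does not appear among the exclusions. The nearest general safeguard is the inclusion item "Stable clinical condition", which is not defined further.
- **Criteria for discontinuation.** The rule has an upper limit of 35 mmol/l and a lower one: if bicarbonate "falls below 16 mmol/l the patient will have to be excluded from the study for safety reasons". The same section says that a patient who leaves early for any reason "is defined as dropout if the subject has already been randomized", whereas one who leaves before randomisation is a screening failure.
- **Statistical analysis.** The analysis population needs a baseline value and at least one follow-up value.

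**The concern.** Bicarbonate defines the condition under study and decides dose titration at visit 3, yet it is bounded on one side only at entry and on both sides afterwards. The lower bound is justified by safety. If a value below 16 mmol/l makes participation unsafe, the same consideration arises on the day of randomisation, and half of those randomised receive placebo.

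Two things are at stake. One is the safety of patients who enter in a range that the plan treats as unsafe. The other is the integrity of the randomised comparison. A patient identified before allocation is a screening failure and costs the trial nothing. The same patient identified after allocation is a dropout, contributes little to a 2-year slope, and comes from the most acidotic part of the population.

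**Working it through.** **1. The two rules side by side**

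| Serum bicarbonate (mmol/l) | Bicarbonate entry criterion | Discontinuation rule |
|---|---|---|
| above 35 | not met by this value | exclude |
| above 22, up to 35 | not met by this value | no action |
| 16 to 22 | met | no action |
| below 16 | met | exclude |

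The last row is the overlap. A value of 15 meets the entry criterion, triggers no listed exclusion, and lies in the range where exclusion is compulsory. Because the qualifying value may be up to 6 months old, the value at randomisation can also differ from it, and no listed criterion tests the later one.

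**2. How many patients (assumed, since the documents give no count)**

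The only anchor is in Background: 58.1% of 823 unselected transplant patients at the sponsor's clinic were below 24 mmol/l. Assumptions: readings are normal; SD 2.5, 3.0 or 3.5; correlation between two readings of one patient 0.6 or 0.8; 1 to 4 readings in the 6 months; no treatment effect.

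- Mean = 24 − SD × z(0.581), with z(0.581) ≈ 0.204. This gives 23.49, 23.39 and 23.28 for the three SDs.
- A patient is eligible if at least one of the prior readings is 22 or less.
- Simulation gives the share of eligible patients below 16 at baseline, and the share below 16 at both baseline and the next reading.

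| SD | Below 16 at baseline, of 300 | Below 16 at baseline and next reading, of 300 |
|---|---|---|
| 2.5 | about 1 | about 0.1 to 0.4 |
| 3.0 | about 4 to 6 | about 1 to 2 |
| 3.5 | about 9 to 16 | about 2 to 6.5 |

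The extreme shares at baseline are 0.3% (SD 2.5, correlation 0.6, 4 readings) and 5.2% (SD 3.5, correlation 0.8, 1 reading); 300 × 0.003 ≈ 1 and 300 × 0.052 ≈ 16. The second column is much smaller because a single extreme reading tends to be followed by a less extreme one.

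**3. Effect on power**

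Inputs from Sample size: 150 per group, difference 3.0, SD 9.0, two-sided 0.05. The standardised difference is 3.0 / 9.0 = 0.333.

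- Plan's figure: 82%. The exact two-sample t-test gives 82.1% and the normal approximation 82.3%. The stated power reproduces.
- Losing 7 of 300 in total (146.5 per group on average): 81.2% by t-test.
- Losing 7 per group (143 per group): 80.2% by t-test, 80.5% by normal approximation.
- Losing 8 per group (142 per group): 79.9% by t-test, 80.2% by normal approximation.

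With about 0 to 7 patients still below 16 at the next reading, power stays at about 81% to 82%, even if all of them were lost entirely.

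**The case against.** The strongest reply is that the rule governs patients already in the study. It stands under discontinuation, and the verb *falls* suggests a drop during follow-up. On that reading one rule covers entry and the other deterioration, and they do not formally conflict. It is a fair reading, but it leaves an inconsistency: a patient who drops to 15 must leave on safety grounds, while one who enters at 15 may stay. The passages need reconciling either way.

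A second reply is that randomisation follows successful screening and requires a stable clinical condition, so an investigator could turn such a patient away, and the full protocol may say more about screening. This lowers the likely number. It does not supply a limit: clinical stability is undefined, and the one quantified stability criterion concerns creatinine. Table 2 is presented as the trial's eligibility criteria and is detailed, so this is an overlap between two stated rules and not a gap left by condensing.

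Three stronger readings are tempting and are not supported.

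- *A patient who enters below 16 is bound to be removed at the next reading.* The next reading may well be above 16, and the wording does not clearly cover someone who has not fallen.
- *The losses would take power below 80%.* Seven lost per group still leaves 80.2%. Only the most extreme assumptions, with all of about 16 patients lost entirely, reach 79.9% by t-test, and the normal approximation stays at 80.2%. A patient with one follow-up eGFR, for example from visit 3 if it is measured there, also stays in the mixed model.
- *The loss will be unbalanced between arms.* The direction is plausible, since alkali should raise bicarbonate, but the documents give nothing from which to calculate its size.

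**Conclusion.** The point holds as an inconsistency between eligibility and the safety rule. As written, a patient can be randomised, possibly to placebo, while already in the range the plan treats as unsafe for participation, and may then become a dropout whom screening could have caught. This part rests on the text alone.

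The size is uncertain and probably small. The counts in the working rest on the assumed normality, SD and correlation, and on an anchor from unselected patients, whereas trial entrants must have stable graft function and no alkali use in the preceding 4 weeks. The upper figures come only from the largest SD. The effect on power is minor. The reasons to act are patient safety, and avoiding exclusions after randomisation that fall on the most acidotic patients.

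**What to change.** The sponsor's clinicians should reconcile Trial design, Table 2 and Criteria for discontinuation on bicarbonate, and state whether the discontinuation limits also apply at entry. The agreed range should then be applied to the sample taken before randomisation, so that nobody is allocated who already meets the exclusion rule. No threshold is proposed here; that is a clinical decision.

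The cost is one eligibility line by amendment and a few more screening failures. The sample size and the analysis model need no change.
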